## Abstract

**Background:**

People who have a transient ischaemic attack (TIA) or minor stroke are at high risk of a recurrent stroke, particularly in the first week after the event. Early initiation of secondary prevention drugs is associated with an 80% reduction in risk of stroke recurrence. This raises the question as to whether these drugs should be given before being seen by a specialist – that is, in primary care or in the emergency department. The aims of the RAPID-TIA pilot trial are to determine the feasibility of a randomised controlled trial, to analyse cost effectiveness and to ask: Should general practitioners and emergency doctors (primary care physicians) initiate secondary preventative measures in addition to aspirin in people they see with suspected TIA or minor stroke at the time of referral to a specialist?

**Methods/Design:**

This is a pilot randomised controlled trial with a sub-study of accuracy of primary care physician diagnosis of TIA. In the pilot trial, we aim to recruit 100 patients from 30 general practices (including out-of-hours general practice centres) and 1 emergency department whom the primary care physician diagnoses with TIA or minor stroke and randomly assign them to usual care (that is, initiation of aspirin and referral to a TIA clinic) or usual care plus additional early initiation of secondary prevention drugs (a blood-pressure lowering protocol, simvastatin 40 mg and dipyridamole 200 mg m/r bd). The primary outcome of the main study will be the number of strokes at 90 days. The diagnostic accuracy sub-study will include these 100 patients and an additional 70 patients in whom the primary care physician thinks the diagnosis of TIA is possible, rather than probable. For the pilot trial, we will report recruitment rate, follow-up rate, a preliminary estimate of the primary event rate and occurrence of any adverse events. For the diagnostic study, we will calculate sensitivity and specificity of primary care physician diagnosis using the final TIA clinic diagnosis as the reference standard.

**Discussion:**

This pilot study will be used to estimate key parameters that are needed to design the main study and to estimate the accuracy of primary care diagnosis of TIA. The planned follow-on trial will have important implications for the initial management of people with suspected TIA.

**Trial registration:**

ISRCTN62019087

## Background

The high risk of stroke following a transient ischaemic attack (TIA) or minor stroke is now well recognised, with an untreated risk of recurrence by 90 days around 18% [1,2]. Much of this excess risk is in the first few days following the initial event [3]. Simple clinical features (an ABCD2 score, based on age, blood pressure (BP), clinical features, diabetes and duration) can identify those people who are at particularly high risk in the first 7 days [4,5]. On this basis, NICE recommends that people at the highest risk of stroke are seen by a specialist within 24 hours of symptom onset (to maximise the chance that risk-modifying treatment is initiated before a further event) and people at lower risk of stroke are seen within 7 days. The National Institute for Health and Care Excellence (NICE) recommends that 300 mg aspirin daily is prescribed while awaiting specialist treatment, but no other secondary prevention treatment is recommended prior to confirmation of diagnosis [6].

Approximately 10,000 recurrent strokes occur within the first 90 days after TIA and minor stroke each year [7]. If rapid primary care initiation of secondary prevention drug treatment could reduce 90-day recurrence rates further from 10% to 2%, this would be equivalent to preventing 8,000 strokes per year. A reduction in the national stroke incidence in this 5% to 10% range would also lead to savings in care costs of the order of £90Mto £180Mper year in England alone, based upon 2005 National Audit Office calculations.

### Evidence that very early treatment reduces recurrent stroke

There is an emerging evidence base as to what treatments will reduce the risk of stroke in the immediate days and weeks following TIA. Aspirin is effective when given as soon as possible [8], and for people with significant carotid artery stenosis, carotid endarterectomy is highly effective as a secondary care surgical procedure: the number of patients that must be treated to prevent one ipsilateral stroke within 5 years’ follow-up is five within a fortnight of the initial stroke or TIA (compared to 125 after 12 weeks) [9].

There is evidence that cholesterol lowering and blood-pressure lowering are effective in the long term with regards to secondary stroke prevention [10,11], but there is uncertainty with regard to their value in the early phase. With regard to cholesterol lowering, there was no evidence of benefit of early administration of simvastatin in the pilot FASTER trial, which comprised patients with a TIA or minor stroke within 24 hours of onset who had been admitted to hospital [12]. Trials of blood-pressure lowering in the acute phase of stroke are ongoing, but their findings may be difficult to apply to people whose symptoms have resolved at the time of treatment initiation (that is, people who have had a TIA or minor stroke).

There is some evidence for dual anti-platelet therapy, with the pilot FASTER trial finding a lower risk of stroke in patients receiving clopidogrel plus aspirin compared to aspirin alone [12], though there was no evidence from the MATCH trial that in the longer term this combination was beneficial, with a significantly higher risk of life-threatening bleeds in the group on combination therapy [13]. There is, however, some evidence of longer-term dual anti-platelet therapy benefit from the ESPRIT and ESPS-2 trials, which found the combination of aspirin and dipyridamole was superior to aspirin alone for the treatment of people randomised within 6months of a TIA or minor stroke [14,15]. The EARLY study found a lower risk of stroke and a lower risk of a composite of stroke, TIA, myocardial infarction, major bleeding and death (hazard ratio 0.73, confidence interval 0.44 to 1.19) in patients started on aspirin and dipyridamole within 24 hours of initial symptoms versus patients started on aspirin within 24 hours with dipyridamole started after 7 days, although the results were not statistically significant [16].

Set against this randomised controlled trial (RCT) evidence of mixed benefit for early initiation of secondary prevention medications, there has been encouraging observational data of the beneficial effect of early use of these drugs from the EXPRESS and SOS-TIA studies [3,17]. In the EXPRESS study, changing the protocol ata specialist TIA clinic whereby secondary prevention drugs (dual anti-platelet therapy, blood-pressure lowering therapy and simvastatin) were commenced on the same day rather than waiting for the general practitioner (GP) to commence treatment on receipt of a clinic letter was associated with an 80% reduction in the risk of stroke at 90 days. The median delay from prescription of first treatment fell from 20 days to 1 day. In the SOS-TIA study, patients with suspected TIA (53% within 24 hours of symptom onset) were seen in a specialist clinic where a stroke prevention programme was initiated. The 90-day risk of stroke in patients treated in this way was about 80% lower than would have been anticipated given their clinical features by applying the ABCD2 score [5].

### Why is a trial of early treatment in primary care necessary?

Many patients with TIA suffer a stroke before they are seen by a specialist, and it is likely that some of these strokes are preventable by earlier initiation of secondary prevention by the first doctor to see the patient, either in primary care or an emergency department.

In the NORTHSTAR study set in five TIA clinics (with a median delay of 15 days from symptom onset to specialist review), the observed 90-day risk of stroke was less than half what it is in studies where patients were seen within the first day [18]. This supports the concept that patients are at highest risk in the period before they encounter a specialist, and therefore the most effective way of preventing a recurrent stroke is for the first doctor who sees the patient to give medication prior to specialist review.

Despite recent advances in access to TIA clinics, the national stroke audit, 2010, reports in its key messages that it is still difficult to achieve appropriate timely access for high risk patients in secondary care:

*High-risk patients are still not being seen quickly enough. A third of centres admit high-risk TIA in order to access specialist assessment, although we know that TIA patients generally sit outside of the acute stroke unit when admitted. Only 10% of centres provide a seven day a week outpatient based neurovascular clinic for high-risk TIA. Access to carotid imaging for high-risk TIA patients on the same day including the weekend is only possible in 10% of centres. As imaging is an integral part of specialist assessment its low level of provision undermines the benefit of admitting high-risk TIA patients. Almost half of centres admit low-risk TIAs, which is probably a wasteful use of resources*[19].

The proposed trial will investigate the role primary care physicians (PCPs) might play in ensuring rapid treatment – should they give immediate therapy, or simply ensure prompt referral? The pilot work for the trial will also help develop material of immediate NHS relevance – guidance to primary care physicians on how to diagnose TIA and data on the accuracy of primary care physician diagnosis.

Current NICE guidelines recommend that patients with suspected TIA or minor stroke should not routinely be admitted to hospital and should be assessed by a specialist within 7 days (or 24 hours for people at particularly high risk of stroke on the basis of their ABCD2 score) [6]. This trial will compare rapid primary care initiation of secondary prevention with the current UK standard care as described in the NICE guideline.

### Aims

The aims of the trial are to determine the feasibility of a randomised controlled trial, to analyse cost effectiveness analysis and to ask: Should primary care physicians initiate secondary preventative measures in addition to aspirin in people they see with suspected TIA or minor stroke at the time of referral to a specialist?

Questions to address:

1. Is randomisation at the individual patient level possible?

a. Is individual randomisation practical in the primary care environment?

a. Is there evidence of contamination? That is, what proportion and to what extent do patients randomised to usual care receive the active additional treatment?

2. What sample size (and what number of practices) is required for a future trial?

a. What is the recruitment rate of patients to the trial?

a. What is the follow-up rate throughout the trial?

a. What is the preliminary estimate of the primary event rate (number of strokes at 90 days)?

3. Are proposed outcome measures for a future trial feasible?

4. Werethere any adverse events?

5. How accurate is primary care physician diagnosis of TIA?

## Methods/Design

### Outline of design

A pilot trial will recruit patients with symptoms suggestive of TIA or minor stroke in general practices from the catchment of three hospital TIA clinics (Birmingham, Cambridge and Oxford) and the emergency department in Cambridge (Figure 1). Embedded within this pilot trial will be a diagnostic accuracy study comparing the initial diagnosis made by the primary care physician with the final diagnosis following review and investigation at the specialist clinic. When a primary care physician sees a patient with a history suggestive of TIA, are cord will be made of whether TIA or a minor stroke is probable or possible. All patients will then be referred to the TIA clinic. Probable cases will be invited by the primary care physician to enter the trial and the diagnostic accuracy study; possible cases will be invited to enter the diagnostic accuracy study only. Patients will be allocated by telephone to additional pre-TIA clinic drug treatment and usual care or usual care only, with allocation by a minimisation scheme using the following categories: TIA clinic catchment area, primary care clinic type and ABCD2 score. The TIA clinic will record the final diagnosis and adjust treatment accordingly. ‘Usual care’ implies initiation of aspirin therapy and referral to the specialist TIA clinic. The primary outcome will be the number of strokes at 90 days. Semi-structured interviews will be undertaken with the aim of determining how trial procedures might be modified for the main trial.

**Figure 1 F1:**
[figure not shown]
Cohort diagram of the RAPID-TIA trial.

### Study population

The study population will comprise patients attending general practice, out-of-hours general practice and emergency departments with recent symptoms suggestive of TIA or minor stroke. The primary care physician will assess whether a diagnosis of TIA or minor stroke is probable or possible. The former group will be eligible for the trial. The latter group will not be eligible for the trial, but will be eligible for the diagnostic accuracy study.

### Identification of patients

Eligible patients will be drawn from general practices in the catchment areas of the TIA clinics in Queen Elizabeth Hospital (Birmingham), Walsall Manor Hospital (Birmingham), Addenbrooke’s Hospital (Cambridge) and John Radcliffe Hospital (Oxford), as well as the emergency department in Cambridge. Oxfordshire practices that are participating in the OXVASC study will be excluded from the trial. For the pilot trial, we aim to recruit approximately ten practices from each area and one out-of-hours general practice base from each area.

### Inclusion and exclusion criteria

#### Inclusion criteria

Patients presenting to a primary care physician with symptoms suggestive of TIA or minor stroke (first and recurrent, but only one event per patient in the trial).

#### Exclusion criteria

Patients will be excluded if:

• The PCP considers that immediate emergency admission is required for any reason. This will include patients where symptoms have not substantially resolved by the time they see the PCP. PCPs will record reasons for exclusion.

• The patient has experienced a TIA or stroke within the previous month.

• The PCP is not in equipoise.

### Recruitment

About 3 of the 1,000 people per annum who present with symptoms suggestive of TIA or stroke are not managed as inpatients [7]. Therefore, a practice with a list size of 7,500 will have 20 patients per year that might be referred into the study. If we assume that 5 people per practice per year are actually randomised, this would mean that 30 practices recruiting patients over a 1year period would recruit 150 patients. Additional patients will be recruited via out-of-hours general practice services and emergency departments to reach a recruitment target of 170, of whom we estimate 100 will be recruited to the trial, and an additional 70 patients to the diagnostic accuracy study only.

### Patient information and consent

Patients who are suspected of having a probable TIA or minor stroke will receive information sheet A and be invited to enter the pilot trial and diagnostic study. Patients who are suspected as having a possible TIA or minor stroke will receive information sheet B and be invited to enter the diagnostic study only. Patients will be given time to consider the information and to ask questions. If the patient declines to enter the pilot or diagnostic study, usual care will proceed. If the patient accepts the invitation, usual care will proceed alongside an assessment of eligibility for the trial. The primary care physician will obtain written consent from eligible patients who are willing to take part in either study.

### Randomisation

Telephone and internet randomisation will be available utilising the resources of the Robertson Centre for Biostatistics, part of the Glasgow Clinical Trials Unit. During the pilot phase, a minimisation scheme will be utilised across the whole trial, using the following minimisation factors: TIA clinic catchment area (Birmingham, Cambridge or Oxford), clinic type (general practice, out-of-hours general practice or emergency department) and risk of stroke using the ABCD2 score (4 or more; less than 4). When an eligible patient has given written consent to take part, the primary care physician will ring the dedicated randomisation number of the Clinical Trials Unit. Patient and site information will be given to the trials unit who will assign the patient to additional treatment plus usual care or usual care only.

### Sample size

This pilot study will be used to estimate the sample size required for a future RCT. The diagnostic accuracy study embedded within this pilot study requires a sample size of approximately 100 probable cases and 67 possible cases. GP diagnosis will be compared to TIA clinic diagnosis in the light of relevant investigations. We will not only be able to report on the predictive value of GP diagnosis, but also sensitivity and specificity since the ‘possible’ TIAs will also be referred to the clinic (although they will not take part in the clinical trial). If we have 100 probable and 67 possible cases referred, and assume sensitivity around 80%, predictive value of around 67% and specificity around 60% from our previous work on modelling the impact of different patterns of TIA services [20], then the confidence intervals will be between +/−10% for each of these parameters.

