### Diagnostic accuracy study

All patients who consent will be entered into the diagnostic study; patients with a diagnosis of possible TIA or minor stroke will be entered only into the diagnostic study.

The primary care physician will complete the usual local TIA clinic referral form. In addition, the PCP will record the presence or absence of symptoms, signs and past medical history relevant to the diagnosis of TIA, including individual features to enable the ABCD2 score to be calculated: age, blood pressure, clinical features including presence of unilateral weakness and speech impairment, duration of symptoms and diabetes [5]. The PCP will provide a level of certainty of diagnosis based upon clinical judgement: probable or possible.

All patients will then be referred to a specialist clinic as per NICE guidelines (with the degree of urgency dictated by the ABCD2 score) [6]. At the TIA clinic, the diagnosis, ABCD2 score and clinical features will be recorded. Patients will be asked to give consent that their clinical notes can be reviewed to ascertain their final diagnosis (as a final diagnosis may not be reached at the initial specialist appointment).

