Given that PCPs currently refer a high proportion of patients without TIA to TIA clinics (threatening to increase the sample size requirement), this pilot study will estimate the proportion of patients with TIA who are likely to be referred in the main trial, and gather evidence to support improved diagnostic accuracy in primary care. Currently diagnostic or referral support tools have not been trialled in primary care and as such there is no current evidence base to inform an intervention to improve the diagnostic accuracy of TIA referrals from PCPs. Within the pilot study, referring PCPs will have a choice as to whether to diagnose patients as probable TIA or minor stroke (and enter them into the treatment trial) or as possible TIA or minor stroke (and not enter them into the treatment trial). It is likely that this choice will mean that more than 50% of patients entered into the treatment trial will have experienced a TIA or minor stroke, and this pilot study will gather data on whether diagnostic accuracy is higher in the “probable TIA” group.

This pilot study will therefore both test the feasibility of the main study and provide novel data on diagnostic accuracy in primary care and the primary care recorded clinical features that are associated with a positive specialist diagnosis. The main study will inform national stroke prevention policy in patients with suspected TIA and contribute significantly to the evidence base for managing TIA in primary care.

The study so far has experienced some difficulties. Recruitment occurred in real time and this can prove difficult depending on the demands the PCP is experiencing at the time of recruitment, such as a late-running clinic. This led to patients meeting the inclusion criteria being missed. We are also experiencing low recruitment rates. To try to understand why this is occurring we are carrying out audits on the participating GP practices, as well as the participating TIA clinics, to enable us to quantify the reasons why patients were not recruited into the study.

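### The diagnostic study can give sensitivity and specificity only for a probable-versus-possible label among suspected, referred patients, not for primary care diagnosis of TIA in general

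*Protocol article*

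**What the plan says.** The Abstract (Methods/Design) of the protocol article promises that "we will calculate sensitivity and specificity of primary care physician diagnosis using the final TIA clinic diagnosis as the reference standard". Question 5 under Aims asks, without restriction, how accurate the physician's diagnosis of TIA is. The Sample size section says "We will not only be able to report on the predictive value of GP diagnosis, but also sensitivity and specificity since the" *possible* cases will also go to the clinic.

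The index test has two levels. Study population: "The primary care physician will assess whether a diagnosis of TIA or minor stroke is probable or possible". Diagnostic accuracy study: "The PCP will provide a level of certainty of diagnosis based upon clinical judgement: probable or possible". The inclusion criterion requires symptoms that suggest TIA or minor stroke, and Outline of design has both label groups referred to the clinic.

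On size, the diagnostic study "requires a sample size of approximately 100 probable cases and 67 possible cases". The authors "assume sensitivity around 80%, predictive value of around 67% and specificity around 60" per cent, and conclude: "then the confidence intervals will be between +/−10% for each of these parameters".

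The Discussion adds that "this pilot study will gather data on whether diagnostic accuracy is higher in the" *probable* group.

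**The concern.** Sensitivity is the share of all TIAs that the physician calls positive. Specificity is the share of all non-TIAs that the physician calls negative. Both need patients whom the physician judged not to have TIA, and the article describes no such group. A *possible* patient is one the physician suspects and refers, yet that patient fills the negative row of the table. A TIA labelled *possible* then counts as a false negative although it was suspected and sent to the clinic. A TIA that the physician dismissed counts nowhere, and nor does a non-TIA that was rightly dismissed.

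What is at stake is the answer to Question 5. The article's background section on why a primary care trial is needed presents data on the accuracy of primary care diagnosis as something of immediate use to the NHS. Figures published under the unrestricted label could be taken as the rate at which primary care misses TIA, which this sample does not measure.

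**Working it through.** **Inputs** (Sample size section): 100 *probable*, 67 *possible*, sensitivity 0.80, predictive value 0.67, specificity 0.60. The confidence level is not stated there; I assume 95%.

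**1. Reproduce the plan, with *probable* as positive and *possible* as negative.**
- True positives = 100 × 0.67 = 67; false positives = 33.
- TIAs in the table = 67 / 0.80 = 83.75; false negatives = 83.75 − 67 = 16.75.
- True negatives = 67 − 16.75 = 50.25; non-TIAs = 33 + 50.25 = 83.25.
- Specificity = 50.25 / 83.25 = 60.4%, against the stated 60%.
- In reverse, specificity of exactly 0.60 needs 33 × 0.6/0.4 = 49.5 true negatives, hence 16.75 + 49.5 = 66.25 *possible* cases, against the stated 67.
- Prevalence = 83.75 / 167 = 50.1%, in line with the Discussion's figure of about half of clinic referrals.

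| | TIA or minor stroke | Neither | Total |
|---|---|---|---|
| *Probable* | 67 | 33 | 100 |
| *Possible* | 16.75 | 50.25 | 67 |
| Judged not TIA | not enrolled | not enrolled | – |

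The inputs agree with one another, and they do so with *possible* as the negative result.

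**2. Precision.** Wald half-width = 1.96 × √(p(1 − p)/n):
- sensitivity: p = 0.80, n = 83.75, ±8.6 points;
- predictive value: p = 0.67, n = 100, ±9.2 points;
- specificity: p = 0.60, n = 83.25, ±10.5 points.

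The claimed ±10 holds to within rounding. Precision is not the problem.

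**3. Effect of the missing row.** Let u be the number of TIAs the physician dismissed and v the number of non-TIAs rightly dismissed. For the threshold *probable*:
- sensitivity = 67 / (83.75 + u), which is below 80% for any u > 0;
- specificity = (50.25 + v) / (83.25 + v), which is above 60.4% for any v > 0;
- predictive value = 67 / 100, which contains neither u nor v.

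The article gives neither u nor v. The values below are assumptions, for illustration only:
- u = 5: 67/88.75 = 75.5%; u = 10: 67/93.75 = 71.5%; u = 20: 67/103.75 = 64.6%.
- v = 50: 100.25/133.25 = 75.2%; v = 100: 150.25/183.25 = 82.0%.

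A wider assumed range, with 67 to 500 dismissed patients of whom 0 to 10% had a TIA, puts sensitivity between 50% and 80% and specificity between 77% and 94%. The directions follow from the formulas. The sizes follow from the assumptions.

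**4. What the sample estimates without this difficulty.** The confirmed proportion is 67/100 = 67% in *probable* and 16.75/67 = 25% in *possible*, with half-widths of 9.2 and 10.4 points. The difference is 42 points, with half-width 1.96 × √(0.67 × 0.33/100 + 0.25 × 0.75/67) = 13.9 points.

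**The case against.** The strongest reply is that the table can be filled. Every enrolled patient is referred and is to receive a final clinic diagnosis, so all four cells for *probable* versus *possible* are observed. Referring the *possible* group is exactly what supplies the false negatives and true negatives, so the reason given in the Sample size section is correct for that table. This stands. A reader might infer that the design can deliver no sensitivity or specificity at all, but the article does not support that.

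The choice of negative is also reasonable. *Probable* is the threshold for entering the treatment trial, and at that threshold a TIA labelled *possible* is a false negative. Scoring any suspicion as positive would force 100% sensitivity and 0% specificity in this sample, but the article proposes that nowhere.

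A further reply is that the restriction is already visible: the Abstract describes the two groups, and the outcome list for the diagnostic study compares the clinic's diagnosis with the two labels. A careful reader can work it out. The promised quantity and Question 5 still carry no restriction.

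A reader might also infer that the Discussion contradicts the Sample size section. Scored as there, 67% of *probable* and 75% of *possible* labels are correct (50.25/67), which would reverse the comparison. The surrounding text, however, concerns the proportion of trial entrants who truly had a TIA or minor stroke, so the phrase is best read as the proportion confirmed. That wording could be clearer but is not a contradiction.

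Finally, the absence of a dismissed group is inferred from there being no third label; the article does not state it. The audits under Recruitment rate take basic data on excluded or missed patients and obtain diagnoses through the TIA clinics. They could find a dismissed patient who reached a clinic another way, but they give no reference diagnosis to one who never did.

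**Conclusion.** The concern holds as a mislabelled quantity. The design estimates the sensitivity and specificity of the label *probable* against *possible* among patients the physician suspects and refers, at about the stated precision. The Abstract, the Sample size section and Question 5 present this as the accuracy of the physician's diagnosis without that limit.

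Taken as the general figure, specificity is understated if any non-TIA was correctly dismissed, and sensitivity is overstated if any TIA was dismissed. The size cannot be derived from the article; the illustrations above rest on assumed counts. More patients of the same two kinds would not remove the difference. The predictive value of *probable* is untouched, as is the randomised comparison.

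A reader might infer that the pilot will show physicians missing 20% of TIAs. The article does not support this: 80% and 60% are planning assumptions, and the 16.75 implied false negatives were all suspected and referred.

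**What to change.** 1. In the Abstract and Sample size section, name the quantity as the sensitivity and specificity of a *probable* (v *possible*) label among patients the physician suspects and refers.
2. State in both places that unsuspected TIAs and correctly dismissed non-TIAs are not captured.
3. Keep the clause that explains why referral of *possible* cases makes the calculation available, but limit it to this conditional quantity.
4. Make the lead answer to Question 5 the proportion with clinic-confirmed TIA or minor stroke in each label group, with 95% confidence intervals, and their difference.
5. For clarity, word the Discussion's comparison as the difference between those two proportions.

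The cost is text only. No extra patients or data are needed, so the change remains possible although the Trial status section reports recruitment as closed. The downside is a narrower and less favourable claim.
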